**Fig. 1 Fig1:**
[figure not shown]
TEEN-BEST flowchart and participant timeline. RYGB = Roux-en-Y Gastric Bypass, SG = Sleeve Gastrectomy, DEXA-scan = Dual-energy X-ray Absorptiometry scan

The trial consists of two phases. Phase 1 will be an internal pilot of twenty patients at each of the two initiating surgical sites (10 + 10 SG and 10 + 10 RYGB in total) to establish feasibility. The methods of recruitment and informed consent will be refined over this period. Phase 2 will be the full multicenter RCT. Patients will be recruited starting in May 2020 until May 2023. Follow-up within the RCT will be planned for a minimum of 5 years.

A matched group, identified from historical data in the multimodal lifestyle intervention program (COACH) of Maastricht University Medical Center, will be used as a non-surgical comparator to the bariatric procedures.

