
### Sample size calculation

A clinical successful weight loss is defined as a TBW loss of ≥20% for this study. We obtained unpublished summary statistics from the Teen-LABS study group, which were used to inform the power calculation. The proportion of participants losing at least 20% of their total body weight at 3 years in the Teen-LABS study was 63% after SG and 72% after RYGB.

The power calculation requires the estimation of two parameters, i.e. the mean TBW loss of participants at 3 years and the difference in mean TBW loss that would be considered clinically important (the non-inferiority margin). The hypothesis is that 70% of the participants will achieve a TBW loss of 20%. The non-inferiority margin was chosen on the basis of the opinions of the clinical applicants and was set at 20%.

A group sample size of 132 patients/arm, allowing for a 15% dropout, is needed to achieve 90% power to detect non-inferiority using a one-sided Z-test (unpooled). The non-inferiority margin is − 0.20000. The true difference between the means is assumed to be 0. The significance level (alpha) of the test is 0.02500.

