Secondary parameters, including quality of life questionnaire scores and other continuous outcomes measured at multiple time points, will be compared using a mixed regression model with baseline and post-surgery measures modeled jointly. Changes in treatment effect with time will be assessed by adding a treatment by time interaction to the model and comparing models using a likelihood ratio test. Time to event outcomes will be compared using survival methods for interval censored data. Frequencies of adverse events will be described. Treatment differences will be reported with 95% confidence intervals (CIs). A detailed analysis plan will be prepared during the feasibility phase 1.

We will compare outcomes between groups at the end of phase 1. Other interim analyses will be decided in discussion with the data safety monitoring committee (DSMC).

In addition, one subgroup analysis is planned; outcomes will be described for male and female participants. Differences in treatment effect between the two subgroups will be tested by including interaction terms to the analysis model.

Missing data will be excluded and will not be imputed. To address possible bias of the missing values, the baseline characteristics of patients with and without missing values will be compared. We will do our utmost to collect outcome measures wherever possible to minimize the number of missing values. This means we will also accept patient reported weight in case of missing weight data. In addition, we will try to retrieve the reason for the missing value, such as missing because of weight gain.

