### Monitoring

The DSMC will review the data periodically regarding the safety and efficacy of the trial procedures and advise the sponsor on the future management of the trial. They will review any unexpected adverse event and may ask to review outcomes or other data that may have an impact on the trial.

They will perform interim analyses, can decide to end the study prematurely and will send their advice to the sponsor of the study. Should the sponsor decide not to fully implement the advice of the DSMC, the sponsor will send the advice to the reviewing REC, including a note to substantiate why the advice of the DSMC (or part thereof) will not be followed.

Independence is a key characteristic of this committee, where the committee members are completely uninvolved in the running of the trial and the committee members cannot be unfairly influenced by people or institutions involved in the trial. The members of the DSMC will reflect the disciplines necessary to interpret the data from the trial; an epidemiologist/statistician, a surgeon, a pediatrician and a bariatric surgeon with experience in adolescents.

All adverse events (AE), related to the bariatric surgery, reported spontaneously by the subject or observed by the investigator or his staff and are unexpected, and serious adverse events (SAE) will be recorded and reported to the sponsor by the main coordinating investigator in accordance with the International Conference for Harmonization of Good Clinical Practice guidelines and the Sponsor’s Research Related Adverse Event Reporting Policy. Abnormalities in blood- and urine samples will only be noted as an AE in case intervention is required. SAEs that are critical to the safety evaluation of the participant need to be reported directly (within 24 h) to the main coordinating investigator. The sponsor will report the AEs/SAEs to the Research Ethics Committee (REC) within 7 days (death or life-threatening) or within fifteen days.

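### The investigators are to compare outcomes between arms at the end of the feasibility pilot, which puts comparative data in the hands of the team that is still recruiting

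*Protocol article*

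**What the plan says.** All places are in the Protocol article.

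- **Trial design:** "Phase 1 will be an internal pilot of twenty patients at each of the two initiating surgical sites". That is 20 patients per arm, 40 in all. The stated purpose is feasibility, and recruitment and consent methods are to be refined. Phase 2, the full multicenter trial, follows. Recruitment runs from May 2020 to May 2023.
- **Data collection, data management and data analysis:** "We will compare outcomes between groups at the end of phase 1". The next sentence reads "Other interim analyses will be decided in discussion with the data safety monitoring committee", so the pilot comparison is itself treated as an interim analysis. The primary analysis is by intention to treat and covers every randomized patient. A detailed analysis plan is to be written during phase 1.
- **Informed consent procedure** and **Randomization:** the coordinating investigator holds the consent conversation and performs the randomization.
- **Monitoring:** the DSMC reviews safety and efficacy periodically. "They will perform interim analyses, can decide to end the study prematurely", and it sends its advice to the sponsor. Its independence from the running of the trial is described as essential.
- **Sample size calculation:** "A group sample size of 132 patients/arm, allowing for a 15% dropout, is needed to achieve 90% power", for a one-sided test. "The significance level (alpha) of the test is 0.02500".

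**The concern.** A feasibility pilot needs counts of patients approached, consented, operated and followed. None of these requires a comparison of the arms. As written, the comparison is made by the authors, covers unspecified outcomes, and takes place while most of the trial is still to be recruited.

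The results could then act on the rest of the trial in several ways:

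- who is put forward and how the trial is presented at consent;
- how readily a patient is moved to the other procedure after randomization (the article plans an as-treated analysis because it expects some switching);
- how hard each arm is followed up, which matters because missing outcomes are excluded and not imputed.

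In a non-inferiority trial analysed by intention to treat, switching tends to pull the arms together, which favours the hypothesis. An investigator-run look also bypasses the independence that the Monitoring section requires of the DSMC.

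A secondary question is whether later DSMC looks fit a design that uses the whole 0.025 in one final test.

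**Working it through.** **1. How much of the trial lies after the look.** The pilot has 40 patients: 40/264 = 15% of the total. The remaining 264 − 40 = 224 (85%) are recruited afterwards, with the coordinating investigator taking consent and randomizing. The 40 pilot patients stay in the primary analysis.

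**2. Can the look include the primary endpoint?** The endpoint is measured 3 years after surgery. With recruitment from May 2020, the first 3-year result falls no earlier than May 2020 + 3 years = May 2023, when recruitment closes. If the dates are read as covering phase 2 only, phase 1 would have to lie between ethics approval on 5 June 2018 and May 2020. That is under two years, again too short. Either way a look before or during phase 2 recruitment has zero information on the primary endpoint and must use earlier outcomes.

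**3. What 20 per arm can show.** For a binary outcome with rate p in both arms, the 95% half-width for the difference is 1.96 × √(2p(1−p)/20). The rates below are assumptions, since the outcomes to be compared are not named:

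- p = 0.10: 1.96 × √(0.18/20) = 0.19
- p = 0.50: 1.96 × √(0.50/20) = 0.31
- p = 0.70: 1.96 × √(0.42/20) = 0.28

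Intervals of about ±19 to ±31 points say little, but a chance difference within them could still sway opinion.

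**4. The plan's own sample size.** Inputs from Sample size calculation: 70% success in both arms, margin 0.20, one-sided alpha 0.025, power 90%, dropout 15%.

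- n = (1.960 + 1.282)² × (2 × 0.7 × 0.3)/0.20² = 110.3, so 111 evaluable per arm.
- 111/0.85 = 130.6, so 131 per arm, against 132 stated. With 112 evaluable, 112/0.85 = 131.8, so exactly 132, and power is 90.4%.

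The figure reproduces as a design with a single test that uses the whole 0.025.

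**5. Later looks at 3-year data.** On the stated dates these data accrue from about May 2023 to May 2026, so DSMC looks at the primary endpoint are possible then. The article gives no schedule, so the following are assumptions. Suppose every look could declare non-inferiority at one-sided 0.025 (Z > 1.96). The statistics at information fractions tᵢ < tⱼ have correlation √(tᵢ/tⱼ), and the overall error is the chance that any of them exceeds 1.96 when the true difference equals the margin.

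- One look at 50% plus the final (correlation 0.707): 0.042, or 0.0416/0.025 = 1.7 times the stated level.
- Looks at 1/3 and 2/3 plus the final (correlations 0.707, 0.577, 0.816): 0.054, or 0.0536/0.025 = 2.1 times.

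**The case against.** Several stronger readings are tempting, and the article does not support them.

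- **The pilot look spends alpha.** Treating it as a test of the primary endpoint at 15% information would give an overall error of 0.047, or 0.060 with a further look at 50%. Step 2 shows that the look carries no primary-endpoint information, so neither figure applies.
- **The trial can stop on efficacy.** This is inferred by joining efficacy review to the power to end the study. No such rule is written. Stopping for safety or futility does not raise the false non-inferiority rate. Recruitment would be over before 3-year data accrue, so an early stop would mainly shorten follow-up.
- **Boundaries are missing.** They may stand in an analysis plan or DSMC charter that is not shown, so their absence is no finding. Interim looks are also compatible with a final level at or near 0.025: an O'Brien-Fleming-type boundary would leave 0.0240 for the final test with one look at 50%, or 0.0225 with looks at 1/3 and 2/3.
- **The analysis plan is still open when the comparison is made.** The text places the plan during phase 1 and the comparison at its end. The only gap is that nothing says the plan is signed first.
- **The margin or endpoint could be reshaped.** Both are published, and substantial amendments need ethics approval and are reported to the register.

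It can also be said that surgeons already know each patient's procedure and that body weight is an objective outcome. That is true, but knowing individual allocations is different from seeing a tabulated comparison of the arms. All these points narrow the concern. None explains why the investigators need a between-arm comparison at the end of a feasibility phase.

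**Conclusion.** The concern holds as one about release of comparative data. Followed as written, the article gives between-arm results to the people who recruit, consent and randomize, with about 85% of the patients still to come. The harm is to equipoise, selection and conduct. Its size cannot be computed from the document. The conclusion assumes that phase 1 ends before or during the main recruitment, as its purpose of refining recruitment and consent implies.

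The alpha point is secondary and conditional. The 0.025 is correct for the single test on which the sample size rests, and 132 per arm is not in error. The error would rise to about 0.042 or 0.054 only under the assumed schedules in step 5, with each look able to declare non-inferiority at 0.025. A reader might infer from the Monitoring section that such stopping is planned, but the text does not say so. It should be corrected because the wording change is nearly free.

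**What to change.** Replace the sentence on comparing groups at the end of phase 1 with:

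> At the end of phase 1 the investigators review only feasibility measures pooled over arms (recruitment, consent, retention, data completeness). Any between-arm data go to the DSMC in closed session, and the analysis plan is signed before any comparative data are seen. The trial will not be stopped early to claim non-inferiority, so the final test stays at one-sided 0.025.

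The Monitoring section and the DSMC charter should say the same. If the sponsor does want the option of stopping for non-inferiority, the last sentence should instead name the boundary, its sidedness and the final level. For example, a Haybittle-Peto rule at one-sided 0.0005 for interim looks, with 0.025 at the end, gives an overall error of about 0.0251 with one look at 50% and 0.0253 with looks at 1/3 and 2/3.

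The cost is wording only, with no added patients. The investigators give up an early comparative look that carries little information.

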### Outcomes

#### Primary outcome measure (non-inferiority)

The proportion of patients that achieve a TBW loss of at least 20% at 3 years after surgery.

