### Data collection, data management and data analysis

After written informed consent is obtained, all patients will be assigned a study number. This moment is defined as baseline; the date when the participant is examined and found suitable to be randomized. Data will be pseudonymous inserted into a computerized database, Research Manager Software (certified by the ‘Information Security Management System 27001’), by local investigators. All data will be handled confidentially, anonymously and in accordance with the international accepted Personal Data Protection Act. A subject identification list will be drafted. This list will be password protected. The subject identification list and the password will be administered by the coordinating and principal investigator.

The follow-up of patients that withdrew from the study will continue according to the implemented standard care for adults who underwent bariatric surgery. This actually means that the follow-up just continues according to the follow-up schedule of the study, because the follow-up in the study is according to the standard care (including laboratory assays and quality of life assessment) for adults.

Primary analyses will be based on intention-to-treat and will include all randomized patients. In addition, a per-protocol analysis will be performed to explore the influence of protocol deviations and compare the results with the primary analysis. Furthermore, to explore the influence of contamination (switching between study arms) we will perform an as-treated analysis, the results of which will be compared with the results of the primary analysis.

The primary parameter, the proportion of patients achieving at least 20% TBW loss at 3 years, will be compared using descriptive statistics and a logistic regression analysis.

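### The primary analysis is declared intention-to-treat on all randomised patients, but the fixed rule to exclude missing data makes the 3-year comparison an available-case analysis

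*Protocol article*

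**What the plan says.** All the analysis rules are in the section on data collection, data management and data analysis of the protocol article.

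- Population: "Primary analyses will be based on intention-to-treat and will include all randomized patients".
- Missing values: "Missing data will be excluded and will not be imputed".
- Bias check: "the baseline characteristics of patients with and without missing values will be compared".
- Reasons: "we will try to retrieve the reason for the missing value, such as missing because of weight gain".
- Steps that reduce missingness: "we will also accept patient reported weight in case of missing weight data". For patients who withdraw: "This actually means that the follow-up just continues according to the follow-up schedule of the study".

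The primary outcome is the proportion with at least 20% total body weight loss at 3 years, compared by descriptive statistics and logistic regression. Per-protocol and as-treated analyses are also planned. They address protocol deviations and switching between arms, not missing outcomes. The sample size section allows for 15% dropout, with 132 patients per arm.

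**The concern.** A patient with no 3-year weight has no value for a single binary endpoint. If that patient is excluded, the analysis no longer includes all randomised patients. The two sentences therefore describe different analyses, and the exclusion rule decides what is actually done. This is a stated rule, not a gap left to the later analysis plan, and a plan that follows the article would inherit it.

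The rule matters because weight determines the endpoint, and weight gain is the article's own example of why a value might be missing. If availability of the 3-year weight depends on weight after surgery, the completers' success rates differ from those of the randomised groups. Unless that distortion cancels between arms, the estimated difference shifts relative to the margin of -0.20. Non-inferiority could then be declared too often, or missed when true. A comparison of baseline characteristics cannot show this, because the selection happens after baseline. The 15% dropout allowance protects power, not validity.

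**Working it through.** **Inputs from the article.** 132 per arm, 15% dropout, 70% success assumed in both arms, margin 20 percentage points, one-sided alpha 0.025, 90% power, unpooled Z-test.

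**The plan's own figure.** n = (1.960 + 1.282)² × 2 × 0.70 × 0.30 / 0.20² = 110.3, so 111 evaluable per arm. 111/0.85 = 130.6, or 131; 112/0.85 = 131.8, or 132. The stated 132 is reproduced. Power with 112 evaluable per arm is 90.4%. About 20 patients per arm, or 40 of 264, may have no outcome.

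**Effect of exclusion at the margin.** The missingness patterns below are assumptions; the documents give none. True success is set at 50% SG and 70% RYGB, so the true difference is exactly -20 points and a correct test declares non-inferiority 2.5% of the time. In each arm, let p be true success, m the share missing and s the success rate among the missing.

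- Completers' success = (p − m·s)/(1 − m)
- Bias = (SG completers − RYGB completers) + 0.20
- Standard error (SE): unpooled, on 132 × (1 − m) patients per arm
- False non-inferiority rate = Φ(bias/SE − 1.96)

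Example with 20% SG and 10% RYGB missing, and s = 30%/50%:
- SG: (0.50 − 0.20 × 0.30)/0.80 = 0.550
- RYGB: (0.70 − 0.10 × 0.50)/0.90 = 0.722
- Difference −0.172, bias +0.028, SE 0.0635
- Φ(0.028/0.0635 − 1.96) = Φ(−1.52) = 6.4%

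| Missing SG/RYGB | Success among missing SG/RYGB | Bias (points) | False non-inferiority |
|---|---|---|---|
| 20%/10% | 30%/50% | +2.8 | 6.4% |
| 20%/10% | 20%/40% | +4.2 | 9.7% |
| 15%/15% | 30%/50% or 20%/40% | 0.0 | 2.5% |
| 10%/20% | 30%/50% | −2.8 | 0.8% |
| 10%/20% | 20%/40% | −4.2 | 0.4% |
| 15%/15% | 30%/30% | −3.5 | 0.6% |
| 15%/15% | 20%/60% | +3.5 | 8.0% |

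The first five rows show that, with those success rates among the missing, the imbalance in missingness drives the result. The last two show that equal missingness is no guarantee: the error can move either way if the gap in success among the missing differs from the true 20-point gap.

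**Missingness driven by outcome alone.** Suppose 5% of successes and 30% of failures are missing in both arms. Then 17.5% of SG and 12.5% of RYGB patients are missing. Completers' success is 0.475/0.825 = 0.576 and 0.665/0.875 = 0.760. The difference is −0.184, the bias +1.6 points and the false non-inferiority rate 4.4%.

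**Could a decision turn?** Suppose 78/112 succeed in each arm. The available-case 95% interval is −12.0 to +12.0 points, so non-inferiority is declared. Now give the 20 missing RYGB patients 14 successes, making 92/132. With 3/20 successes among missing SG patients the lower limit is −19.8 points; with 2/20 it is −20.5 and non-inferiority is lost. Counting all 40 missing as failures gives −11.9 to +11.9, and it stands.

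**The case against.** The article does more to limit missing data than the exclusion sentence suggests. Follow-up continues after withdrawal, self-reported weights are accepted when no other weight exists, reasons for missing values are sought, and monitoring can focus on sites with many withdrawals. The baseline comparison is therefore not the only safeguard. These steps may leave fewer missing values than the 15% allowed for, which is a planning allowance and not a forecast. They do not say how the patients still missing enter an analysis of all randomised patients.

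A reader might infer that the protocol expects dropout from weight gain, or concedes that its analysis is biased. It does neither: weight gain is an example ("such as missing because of weight gain"), and the text speaks only of possible bias.

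A reader might also infer that exclusion favours non-inferiority. The table does not support that. The 6.4% and 9.7% rest on a 2:1 imbalance in missingness that has no basis in the documents, and reversing it makes the test conservative. Moreover, when missingness depends on outcome alone, the odds ratio from the planned logistic regression is undistorted (0.43 before and after exclusion). The margin, however, is a difference in proportions, and that does shift.

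The primary outcome section times the endpoint "at 3 years after surgery", which might suggest that randomised patients who are never operated on drop out as well. The documents do not say that such patients are expected, and the hypothesis and analysis text refer simply to 3 years. How to date such patients is a matter for the analysis plan.

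Finally, self-reported weights might seem to belong outside the primary analysis. Removing them would create more missing data, so this is a trade-off and not an error.

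**Conclusion.** The contradiction stands. As written, the primary result is an available-case comparison labelled intention-to-treat, and the stated check cannot reveal selection by weight after surgery. Its size and direction are not known. Against a nominal 2.5%, the error at the margin is 6.4% to 9.7% with 20%/10% missing (SG/RYGB), and 2.5% with 15%/15% and the same success rates among the missing. It is 0.4% to 0.8% with 10%/20%, and 4.4% under the outcome-driven pattern. All of these assume true success of 50% and 70%, and missingness patterns that the documents do not give. The tipping-point example needs an extreme contrast between arms. The case for change rests on the conflict between the two rules and on an unprotected primary test, not on a predicted bias towards SG. It should be settled before outcome data are seen.

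**What to change.** Replace the exclusion sentence with a rule along these lines:

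- The primary intention-to-treat analysis includes all randomised patients. Missing 3-year outcomes are multiply imputed by arm from baseline and interim weights, sex and centre.
- Because this imputation assumes missingness at random, it does not by itself deal with dropout caused by unobserved weight gain. Add an analysis counting missing as failure in both arms, and a tipping-point analysis that varies success among the missing separately by arm.
- Keep the complete-case analysis as a sensitivity analysis, under that name.
- Flag patient-reported weights, keep them in the primary analysis, and add a sensitivity analysis without them.

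The cost is a change of wording and modest extra analysis work. The sample size does not change, and no extra patients or visits are needed.
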